### Planned interim analysis

A planned interim analysis will be performed when 155 patients have been recruited to the study and followed-up for a minimum of 3 months. The report will be reviewed by the study steering group and the results will be made available to the study sponsor.

If the overall implant loss rate at 3 months following surgery is 15% or more, the study will be stopped.

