**Methods and analysis:**

Pre-BRA is an IDEAL stage 2a/2b prospective multicentre cohort study with embedded qualitative research.

Consecutive patients electing to undergo immediate PPBR at participating centres will be invited to participate. Demographic, operative, oncology and complication data will be collected and patient-reported outcomes will be assessed at baseline, 3 and 18 months postoperatively. The primary safety endpoint will be implant loss at 3 months.

Surgeons performing PPBR will be asked to complete questionnaires regarding their practice and report any modifications made to the procedure or learning arising from complications via free-text response fields on electronic case-report forms. Semistructured will explore surgeons’ experiences in detail to identify emerging best practice. This will be fed back to participating surgeons to promote shared learning.

The Pre-BRA study will aim to recruit 341 patients from 30 to 40 UK centres over a 12-month period. Recruitment will commence Spring 2019.

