## Data collection

### Clinical data

Demographic, comorbidity and operative data will be collected for each participant via a standardised electronic CRF hosted on REDCap^36^ (online supplementary appendix 2).

10.1136/bmjopen-2019-033641.supp2Supplementary data

Complications and oncological data will be collected at 30 days and 3 months by clinical or case-note review according to local follow-up policies. Details of any additional surgery required for complications or cosmesis will be collected at 18 months by case note review. No additional clinic visits will be required for the study. All complications will be defined a priori using standardised definitions as per previous studies^7 37^ (online supplementary appendix 3)*.*

10.1136/bmjopen-2019-033641.supp3Supplementary data

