### Data analysis and sample size

#### Prepectoral safety and effectiveness

##### Sample size

A single-arm two-stage design will be used to assess the safety of PPBR based on the primary outcome of implant loss rate at 3 months. It is expected that the implant loss rate will be 9% or lower based on findings from the recent iBRA study;^7^ 15% or greater will be deemed unacceptably high.

A sample size of 310 patients would result in a two-sided 95.0% CI for a single proportion, assumed to be 0.10, with a width equal to 0.070. Allowing for a 10% loss to follow-up at 3 months at least 341 patients will be recruited to inform a future trial with implant loss as the primary outcome.

Based on data from the iBRA study, the number of prepectoral reconstructions performed at each site is likely to be small (4–40 per year).^7^ We will therefore aim to recruit from between 20 and 30 sites over a period of 12 months.

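### The single safety look comes when, on planned accrual and without a recruitment pause, about 70% of patients are enrolled; acting at the 24th implant loss would keep the 15% boundary and stop earlier at little cost

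*Protocol article*

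**What the plan says.** The Sample size section describes a single-arm design in two stages, with implant loss at 3 months as the primary outcome. It expects a loss rate of 9% or lower and regards 15% or greater as unacceptable. The Planned interim analysis section sets the one look: "A planned interim analysis will be performed when 155 patients have been recruited to the study and followed-up for a minimum of 3 months". The rule attached to it is: "If the overall implant loss rate at 3 months following surgery is 15% or more, the study will be stopped".

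On size and pace, the Sample size section says "Allowing for a 10% loss to follow-up at 3 months at least 341 patients will be recruited", and the abstract says the study will "aim to recruit 341 patients from 30 to 40 UK centres over a 12-month period". The two places differ on the number of sites (30 to 40 in the abstract, 20 to 30 under Sample size), but both give 12 months.

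Under Clinical data, "Complications and oncological data will be collected at 30 days and 3 months by clinical or case-note review". No stopping rule is tied to the 30-day data. The article describes no other stopping look and no running tally. It does not say whether recruitment pauses or continues while the first 155 are followed.

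**The concern.** A stage-1 look limits stage-2 enrolment only if it arrives before much of stage 2 has been recruited. Here the look needs 155 patients plus a further 3 months, which is a quarter of the planned recruitment period. If sites keep recruiting through those 3 months, much of stage 2 is enrolled before the rule can act.

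The rule can also be met well before the look. The number of implant losses among a fixed set of patients can only rise. Once it reaches the count that satisfies 15% of 155, the result of the scheduled analysis is settled, yet the plan as described still waits for the report. At stake is how early the study stops, and how early participating surgeons are warned, if the loss rate is unacceptably high.

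**Working it through.** **Inputs from the article.** 310 evaluable and 341 recruited (Sample size); 12 months of recruitment (abstract and Sample size); interim at 155 patients with 3 months of follow-up, and stop at 15% or more (Planned interim analysis). The accrual pattern, the reporting lag and the timing of losses within 3 months are not given and are assumptions below.

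**The plan's own figures.**
- The exact (Clopper-Pearson) 95% interval for 31/310 has width 0.06997, which reproduces the stated 0.070.
- 310 × 1.10 = 341.
- 310 / 2 = 155.

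**Enrolment at the scheduled look, uniform accrual, no pause.**
- Rate: 341 / 12 = 28.4 per month.
- Patient 155 enters at 155 / 28.4 = 5.45 months.
- That patient completes 3 months at 5.45 + 3 = 8.45 months.
- Enrolled by then: 8.45 × 28.4 ≈ 240, and 240 / 341 = 70%. About 240 − 155 = 85 enter after patient 155.
- With one month for data return and review: 9.45 × 28.4 ≈ 269 (79%). With two months: 297 (87%).

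**Range under other assumptions.** Cumulative accrual is N(t) = 341 (t/T)^k, where k = 1 is uniform.

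| Assumption | Share enrolled at the look |
|---|---|
| Accrual held at 155 | 155/341 = 45% |
| Uniform over 24 / 18 / 15 months | 58% / 62% / 65.5% |
| Front-loaded, k = 0.5 to 0.8, 12 months | 67.6% to 68.5% |
| Uniform, 12 months | 70% |
| Sites ramping up over 3 / 6 months | 74% / 79% |
| 155 evaluable after 10% loss (about 172 recruited) | 75% |
| Slow start, k = 2 | 85% |

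**The boundary as a count.** 0.15 × 155 = 23.25. So 23/155 = 14.8% continues and 24/155 = 15.5% stops. Loss to follow-up only shrinks the denominator, so 24 losses among the first 155 patients always meet the rule. Acting at the 24th loss therefore never stops a study that the scheduled look would have continued. Keeping the scheduled look catches any stop reached with fewer losses on a smaller denominator.

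**When the 24th loss occurs.** By simulation, with uniform accrual, each loss falling evenly over the 3 months after entry, and medians taken over runs that reach 24 losses. A one-month reporting and review lag adds 28 patients.

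| True loss rate | Median enrolled, no lag | Median, one-month lag | Scheduled look, one-month lag | Fewer enrolled |
|---|---|---|---|---|
| 15% | 185 (10th–90th centile 156–216) | 185 + 28 = 213 | 269 | 56 |
| 20% | 160 (134–193) | 160 + 28 = 188 | 269 | 81 |
| 25% | 138 | 138 + 28 = 166 | 269 | 103 |

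At a true rate of 15% the rule stops the study in about 47% of runs; the binomial probability of 24 or more losses in 155 is 0.467. At 9% it is 0.006. With the first 155 patients as denominator, acting at the 24th loss leaves these probabilities unchanged.

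**The case against.** **Continued recruitment is inferred.** A two-stage design is compatible with a gate between the stages, and this is a journal article condensing a full protocol that is not shown. That stands: 70% holds only if there is no pause.

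**70% is not a floor.** A reader might infer that at least 70% must be enrolled by the look. The article does not support this. The figure is the result for uniform accrual over exactly 12 months; slower or front-loaded accrual gives 58–68%.

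**The study is observational.** A reader might count everyone enrolled before the look as exposed to the operation because of the design. The article does not support that either. Patients have already elected the procedure before they receive the study information, centres already perform it, and surgeons follow their usual practice. Stopping the study does not by itself stop the surgery. This stands and limits the benefit to earlier stopping and earlier warning.

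**The gain depends on reporting.** If losses are recorded only at the existing 30-day and 3-month points, with no further lag, the median trigger is 213 enrolled at a true 15% and 183 at 20%, against 240 for the scheduled look on the same footing. The gain is then smaller but does not vanish. Sites that rely on case-note review would have to report this event as it happens to get the larger gain.

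**The denominator is not fixed.** The rule refers to an overall rate. It could be read as covering all patients with 3-month data, or implants where surgery is bilateral. With more than 160 units (24/160 = 15.0%), 24 losses would fall below 15%. This stands, and it is why the denominator has to be stated first.

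**One look at half the evaluable sample is conventional.** True, and nothing in the section is wrong or contradictory. That argues against calling it an error, not against a cheap improvement.

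**Conclusion.** The point holds as a cheap improvement. On the article's planned 341 patients in 12 months, with uniform accrual and no pause, the only described stopping rule can first act with about 240 (70%) enrolled, or 269 (79%) after one month for review. The same boundary applied at the 24th loss among the first 155 would act about 56, 81 or 103 patients earlier, in median, at true loss rates of 15%, 20% or 25%. That assumes the same one-month lag on both sides, losses spread evenly over 3 months, and a denominator of the first 155 patients. If the full protocol holds accrual at 155, the share is 45%, no further patients are enrolled while the 155 are followed, and most of the benefit disappears.

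It would go too far to conclude that the interim analysis is defective or that the plan cannot work as written: the look is properly defined in time and has a stated boundary. What can be improved is how soon that boundary is acted on.

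**What to change.** In the Planned interim analysis section:

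1. State that the denominator is the first 155 patients, counted per patient.
2. State whether recruitment is held while those patients complete 3 months.
3. If it is not held, have implant losses entered on the electronic case report form as they occur, and trigger steering-group review under the existing 15% rule when the 24th loss among the first 155 patients is recorded. Keep the scheduled analysis as the latest time point.

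The boundary and, with that denominator, the stopping probabilities do not change, and no extra patients or visits are needed. The cost is a few lines of protocol text, a rolling tally at the coordinating centre, and event-driven reporting of one event type by sites that now follow local review schedules.

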### Shared learning and intervention stability feasibility study

Analysis of the free-text responses will be an ongoing and iterative process commencing soon after the study begins and will inform sampling for the semistructured interview phase of the study. Text will be assigned codes and analysed using the constant comparative technique of grounded theory.^39^ A combination of thematic and content analysis will be used to identify common themes.^40 41^ These will inform the topic guide for the interviews and the feedback provided to study participants.

Sampling, data collection and analysis will be undertaken concurrently and iteratively until no new themes emerge from the data.

### Dissemination of best practice and shared learning

The learning and modifications emerging from the CRFs and interviews will be consolidated and reviewed at regular intervals by the study team. Any common themes will be shared with participating surgeons using a combination of methods. These will include a ‘tips and tricks’ section on the study website; e-mail updates; study newsletters and potentially social media channels (eg, ‘You Tube’). The acceptability and value of the different approaches to sharing learning will be discussed with individual surgeons at interview and the wider steering group. Metrics such as number of views/hits for online/social media resources will be used to provide additional information regarding engagement if appropriate.

### Design of the main study

If PPBR is considered safe and data from the screening logs suggests sufficient numbers of PPBR are being performed at participating centres, a consensus meeting with key participating surgeons, steering group members, patients and methodologists will be held to agree the final design for a large-scale pragmatic RCT comparing prepectoral and subpectoral IBBR.

## Dissemination

Results will be analysed and presented at national and international meetings and published in peer-reviewed journals. Findings will be fed back to the surgical community to promote engagement and recruitment to a future RCT.
